**12-month follow-up**			
	MOCA	0-30 points: executive function (0-5 points), naming (0-3 points), memory (0-5 points), attention (0-6 points), calculus (0-3 points), language (0-3 points), orientation (0-6 points), abstractization (0-2 points)	
	MIS	0-15 points	
**24-month follow-up**			
	MOCA	0-30 points: executive function (0-5 points), naming (0-3 points), memory (0-5 points), attention (0-6 points), calculus (0-3 points), language (0-3 points), orientation (0-6 points), abstractization (0-2 points)	
	MIS	0-15 points	
**36-month follow-up**			
	MOCA	0-30 points: executive function (0-5 points), naming (0-3 points), memory (0-5 points), attention (0-6 points), calculus (0-3 points), language (0-3 points), orientation (0-6 points), abstractization (0-2 points)	
	MIS	0-15 points	
**48-month follow-up**			
	MOCA	0-30 points: executive function (0-5 points), naming (0-3 points), memory (0-5 points), attention (0-6 points), calculus (0-3 points), language (0-3 points), orientation (0-6 points), abstractization (0-2 points)	
	MIS	0-15 points	
	BDST	0-14 points	
	FDST	0-16 points	
	TMT-A	0-100 seconds (101 seconds means failed test)	
	TMT-B	0-300 seconds (301 seconds means failed test)	
	DSST	Absolute number of correct answers (maximum 90 correct answers), absolute number of incorrect answers (maximum 90 incorrect answers)	

^a^MOCA: Montreal Cognitive Assessment.

^b^MIS: memory impairment score.

^c^BDST: backward digit span testing.

^d^FDST: forward digit span testing.

^e^TMT: Trail Making Test.

^f^DSST: Digit Symbol Substitution Test.

### Laboratory Procedures and Outcomes

We will obtain the serum from 5 mL of the blood sample of each participant and quantitatively measure serum SAA, Hcy, S100B, BDNF levels. The blood samples will be obtained at baseline. Other blood measurements will be performed at the hospital’s laboratory as part of the visit, and values will be taken from the registry. All the necessary data that will be obtained from blood testing are mentioned in Table 14.

**Table 14 table14:** Blood sample outcomes.

Markers		Measurement unit
**Presumed cognitive biomarkers (serum levels)**		
	SAA^a^	mcg/mL
	Hcy^b^	µmol/L
	BDNF^c^	ng/mL
	S100B^d^	mcg/mL
**Common biomarkers (taken from the hospital registry from the baseline presentation period)**		
	C-reactive protein	mg/dL
	Total hemoglobin	g/dL
	Red blood cell count	number/mm^3^
	Fecal calprotectin	μg/mg
	Triglycerides	mg/dL
	Total cholesterol	mg/dL
	Low-density lipoprotein (LDL) cholesterol	mg/dL
	High-density lipoprotein (HDL) cholesterol	mg/dL
	LDL/HDL ratio	fraction
	Neutrophile-to-lymphocyte (NLR) ratio	fraction
	Erythrocyte sedimentation rate	mm/hour
	Mean corpuscular volume (MCV)	%
	Basal blood glucose	mg/dL
	Fibrinogen	mg/dL
	Lactate dehydrogenase (LDH)	IU/L
	Creatine kinase (CK)	U/L
	CK-MB	% out of total CK

^a^SAA: serum amyloid A.

^b^Hcy: homocysteine.

^c^BDNF: brain-derived neurotrophic factor.

^d^S100B: S100 calcium-binding protein B.

#### Preparation of Serum Samples

The required materials are a serum collection vaccutainer, a fixed-angle centrifuge for 15 mL tubes, 1.5 mL protein low-binding tubes, 100-1000 µL tips, and a cryogenic box.

For serum preparation, after the blood is collected, the tube will be inverted gently, as indicated in the manufacturer’s instructions (in general 5-6 times). The tube will be then left, as indicated in the manufacturer’s instructions (in general 30 minutes), at room temperature to form a blood clot. Next, the tube will be centrifuged at 2000× *g* for 10 minutes at 4 °C, as indicated in the manufacturer’s instructions, and 500 µL of serum will be aliquoted in 1.5 mL protein low binding tubes. The serum aliquots will be immediately frozen at –80 °C until use. No more than 2 freeze-thaw cycles will be allowed. The tube with the blood clot will be discarded in a biohazard waste container.

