In conclusion, IBD is a combination of intestinal barrier dysfunction and intestinal and systemic inflammation. Due to intestinal barrier dysfunction, the intestinal microbiome is affected in the course of the disease or it is the cause of the disease (IBD). Several studies have shown the relationship between the gut–brain axis (GBA) and the development of depression, affective mood disorders, and stress, which might promote the development of cognitive impairment. Systemic inflammation is known to increase cardiovascular risk, which is a risk factor for cognitive impairment. Other risk factors, such as smoking, alcohol consumption, and other diseases, also promote the development of cognitive impairment. Some studies have suggested a link between IBD and cognitive disorders, while other studies have indicated a link between mood disorders and IBD, and still others have suggested a link between mood disorders and cognitive disorders. Therefore, this might be a vicious cycle.

In this study, blood biomarkers, such as SAA (an inflammatory biomarker, a precursor of beta-amyloid plaques in the brain), Hcy (a pro-inflammatory molecule increased in cognitive disorders), S100B (a neuronal structural protein increased in brain injury), and BDNF (decreased in cognitive disorders) were selected in order to validate the hypothesis that these biomarkers could be used as predictive factors for cognitive impairment associated with IBD. As a summary of the basic knowledge that led to the idea of this study, Figure 1 shows the possible implied mechanisms underlying the development of MCI in patients with chronic IBD.

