#### Absolute Quantification of Biomarkers

SAA, Hcy, S100B, and BDNF are biomarkers that will be quantified from the serum samples using standardized solid-phase sandwich enzyme-linked immunosorbent assay (ELISA) kits. Table 15 presents the kits that will be used and their related characteristics.

**Table 15 table15:** ELISA^a^ kits to be used for biomarker quantification.

Biomarker	ELISA kit	Serum volume required (µL)	Kit performance	Assay duration (hours)
SAA^b^	Abclonal catalog # RK04228 or similar	100	Range:0.156-10 ng/mL Sensitivity: <0.071 ng/mL Specificity: 50 ng/mL Intra-assay precision: CV^c^<10% Interassay precision: CV<12%	5.0
Hcy^d^	Assaygenie catalog # HUFI04768 or similar	50	Range: 7.813-500 pmol/mL Sensitivity: <4.688 pmol/mL Specificity: 50 ng/mL Intra-assay precision: CV<8% Interassay precision: CV<10%	2.5
S100B^e^	Abclonal catalog # RK02234 or similar	100	Range: 46.9-3000 pg/ml Sensitivity: <23.5 pg/mL Specificity: 50 ng/mL Intra-assay precision: CV<10% Inter-assay precision: CV<15%	5.0
BDNF^f^	Abclonal catalog # RK00074 or similar	100	Range: 23.4-1500 pg/ml Sensitivity: <6.3 pg/mL Specificity: 50 ng/mL Intra-assay precision: CV<10% Interassay precision: CV<15%	5.0

^a^ELISA: enzyme-linked immunosorbent assay.

^b^SAA: serum amyloid A.

^c^CV: coefficient of variation.

^d^Hcy: homocysteine.

^e^S100B: S100 calcium-binding protein B.

^f^BDNF: brain-derived neurotrophic factor.

The required materials for this procedure are the serum aliquots, ice, a fixed-angle centrifuge for 2 mL tubes, 1.5 mL protein low-binding tubes, tips, pipettes, 15 or 50 mL tubes (depending on the ELISA kit instructions), a 96-well plate shaker (if mentioned by the ELISA kit manufacturer), a 96-well plate mixer with heating (if mentioned by the ELISA kit manufacturer), and a multiplate reader.

Serum aliquots will be thawed on ice and then mixed gently. Samples will be centrifuged at 13000× *g* for 2 minutes at 4°C to remove the cell debris. The volume indicated in the kit manufacturer’s protocol will be taken. The instructions will be used for sample preparation and analysis. Measurements will be made in duplicate.

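### Serum BDNF is a primary laboratory outcome, but platelet count is missing from the list of blood data, so a platelet-driven BDNF difference between IBD and controls could not be recognised.

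*Protocol article*

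**What the plan says.** The Abstract of the protocol article names serum BDNF among the primary laboratory outcomes. Table 1 makes its level, and its association with cognitive scores in IBD compared with healthy controls, part of a primary objective. The Background section gives the reason for choosing it: "BDNF (decreased in cognitive disorders) were selected in order to validate the hypothesis that these biomarkers could be used as predictive factors".

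The matrix is fixed under Absolute Quantification of Biomarkers, where the four markers are described as "biomarkers that will be quantified from the serum samples using standardized solid-phase sandwich enzyme-linked immunosorbent assay (ELISA) kits". Under Preparation of Serum Samples the tube stands, following the tube manufacturer's instructions ("in general 30 minutes), at room temperature to form a blood clot"), and is then spun cold ("the tube will be centrifuged at 2000× *g* for 10 minutes at 4 °C") and frozen.

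On the other blood values, Laboratory Procedures and Outcomes says: "Other blood measurements will be performed at the hospital’s laboratory as part of the visit, and values will be taken from the registry". It then closes the list: "All the necessary data that will be obtained from blood testing are mentioned in Table 14". The common biomarkers in Table 14, "taken from the hospital registry from the baseline presentation period", include haemoglobin, "Red blood cell count", mean corpuscular volume and the neutrophil-to-lymphocyte ratio. Platelet count is not there.

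The analysis section plans t or Wilcoxon rank-sum tests between groups, Pearson correlations between cognitive scores and biomarkers, and regressions on risk factors taken from the questionnaires. None of these mentions platelets.

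**The concern.** Platelets store BDNF and release it when blood clots, so a serum BDNF value partly reflects how many platelets were in the tube. That is general laboratory knowledge; the article does not discuss it. If platelet counts differ between patients with IBD and controls, which is plausible in an inflammatory disease but is an assumption here, serum BDNF would differ for a reason unrelated to cognition.

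The artefact could act in either direction. Higher platelet counts in IBD would raise serum BDNF. That could produce an apparent group difference, or it could cancel a real decrease of the kind the Background associates with cognitive disorders. The same section says the direction of BDNF change in IBD is not established, so no prior expectation would expose an artefact. The BDNF-cognition correlation has the same weakness when the groups are pooled: a platelet-driven group difference in BDNF together with a group difference in cognition gives a correlation with no direct link between the two.

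An uncollected variable cannot be examined afterwards. Table 14 is the only place where platelet count would be expected, and the text presents that table as complete.

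**Working it through.** **Setting the sections side by side**

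1. Primary status of serum BDNF: Abstract and Table 1.
2. Matrix: serum from clotted blood (Preparation of Serum Samples; Absolute Quantification of Biomarkers).
3. Blood data to be collected: Table 14, stated to be all that is necessary. Red-cell values and a white-cell ratio are listed; platelets are not.
4. Adjustment: regressions draw on questionnaire risk factors. Platelet count is neither a questionnaire item nor a listed laboratory value.

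So the plan as written has no data and no analysis that could separate a platelet-driven BDNF difference from another one.

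**The plan's own figure**

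The article gives no sample size or expected difference for BDNF. Its one calculation is for MOCA: 52 cases and 26 controls for a difference of 2 points with SD 3.0. A two-sided 5% test at 80% power with 2:1 allocation gives 54 and 27, and 52 and 26 give about 79% power. That figure reproduces and has no bearing on this point.

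**Illustration on assumed inputs**

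None of the inputs below is in the document, except the group sizes (100 per group planned; 50 per group for the first phase to be published) and the two-sided 5% level.

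Assume that a share s of serum BDNF comes from platelets (50% to 95%), that mean platelet count is higher in IBD by a fraction p (10% to 30%), and that the between-person coefficient of variation of BDNF is 35%. There is no true BDNF effect.

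- Relative shift in BDNF = s × p
- Standardised shift d = (s × p) / 0.35
- Noncentrality = d × √(n/2), with n per group, in a two-sample t-test with 2n − 2 degrees of freedom

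| s | p | s × p | d | P(p<.05), 100 per group | P(p<.05), 50 per group |
|---|---|---|---|---|---|
| any | 0 | 0 | 0 | 5% | 5% |
| 0.50 | 0.10 | 0.05 | 0.14 | 17% | 11% |
| 0.75 | 0.20 | 0.15 | 0.43 | 85% | 56% |
| 0.95 | 0.30 | 0.285 | 0.81 | >99% | 98% |

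Example, middle row at 100 per group: 0.75 × 0.20 = 0.15; 0.15 / 0.35 = 0.43; noncentrality 0.4286 × √50 = 3.03; critical t 1.97; probability 85%.

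A second way to set it up is to let the groups differ in platelet count by D standard deviations and let platelet count correlate r with serum BDNF. The spurious shift is then about D × r. For D from 0.3 to 0.8 and r from 0.2 to 0.6, the shift runs from 0.3 × 0.2 = 0.06 to 0.8 × 0.6 = 0.48 SD. The chance of a significant result is then 7% to 92% at 100 per group and 6% to 66% at 50 per group. With D = 0 it is 5%.

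Both versions show that the result depends wholly on quantities the document does not give. They show what could happen; they do not estimate the bias in this study.

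**The case against.** The strongest reply is that the mechanism comes from outside the document. No section says that platelets hold BDNF or that platelet counts differ in IBD. Clotting is how serum is made, and the preparation is described coherently, so nothing in it is an error or a contradiction. Covariates are commonly left to an analysis plan that is not shown. Testing is deferred until acute flares are over (Table 3), which may narrow any platelet difference. C-reactive protein, sedimentation rate, fibrinogen and faecal calprotectin are collected, so inflammation can be examined in part. And because the routine values come from a registry, platelet counts may be retrievable later.

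Much of this stands. The size of any bias cannot be derived from the documents, and the deferral of flares counts in the plan's favour. Two parts do not answer the point. The omission is not silence left to another document, because the article declares Table 14 to be all the necessary blood data. And inflammatory markers are only an indirect stand-in for platelet count. That the value may be retrievable is a reason to add it now.

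Three stronger readings are tempting, and the documents do not support them.

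- A reader might infer that homocysteine is biased too, through release from blood cells before centrifugation. The same nominal clotting step, of about 30 minutes and guided by the manufacturer, applies to both groups, and platelet count has no bearing on homocysteine.
- A reader might infer that times from draw to centrifugation go unrecorded, or that cases and controls are processed differently. Both would be inferred from silence on detail that belongs in a laboratory manual not shown.
- A reader might infer that the BDNF comparison is already shown to be invalid. It is not; whether platelet counts differ between these groups is unknown.

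**Conclusion.** The point holds in a limited form. A primary laboratory outcome is measured in a matrix whose BDNF content depends on platelets, and the declared list of blood data leaves platelet count out while taking other blood-count values from the same registry. If platelet counts differ between IBD and controls, the planned tests and correlations could show a BDNF difference that is not there or miss one that is, and nothing in the data would reveal it.

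This rests on two premises that the document does not state: that platelets contribute substantially to serum BDNF, and that platelet counts may differ between the groups after flares have been deferred. The illustrative chance of a false BDNF finding at 100 per group, from 17% to nearly 100% under one set of assumptions and from 7% to 92% under another, should be read only as showing that the consequence could be small or large. It is 5% if platelet counts do not differ. The omission merits correction because the remedy is cheap and recruitment is still under way. The clotting procedure itself is not at fault.

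**What to change.** - Add platelet count to the registry values in Table 14, taken where possible from the same blood count as haemoglobin.
- Retrieve it for the 53 patients and 50 controls already recruited, where the registry holds it, and report how many values are missing in each group.
- Report platelet count by group at baseline.
- Report the BDNF group comparison and the BDNF-cognition models both unadjusted and with platelet count as a covariate. Keep both, because platelet count may itself be a consequence of IBD: the adjusted result shows how much of a BDNF difference is left at equal platelet count, and the unadjusted result shows the total difference.

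The cost is one further registry value per participant, some missing values (perhaps more often in controls, if their routine blood tests are less complete) and one extra model term. No change to sample handling is needed for this point.

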#### Absolute Quantification of Biomarkers

SAA, Hcy, S100B, and BDNF are biomarkers that will be quantified from the serum samples using standardized solid-phase sandwich enzyme-linked immunosorbent assay (ELISA) kits. Table 15 presents the kits that will be used and their related characteristics.

**Table 15 table15:** ELISA^a^ kits to be used for biomarker quantification.

Biomarker	ELISA kit	Serum volume required (µL)	Kit performance	Assay duration (hours)
SAA^b^	Abclonal catalog # RK04228 or similar	100	Range:0.156-10 ng/mL Sensitivity: <0.071 ng/mL Specificity: 50 ng/mL Intra-assay precision: CV^c^<10% Interassay precision: CV<12%	5.0
Hcy^d^	Assaygenie catalog # HUFI04768 or similar	50	Range: 7.813-500 pmol/mL Sensitivity: <4.688 pmol/mL Specificity: 50 ng/mL Intra-assay precision: CV<8% Interassay precision: CV<10%	2.5
S100B^e^	Abclonal catalog # RK02234 or similar	100	Range: 46.9-3000 pg/ml Sensitivity: <23.5 pg/mL Specificity: 50 ng/mL Intra-assay precision: CV<10% Inter-assay precision: CV<15%	5.0
BDNF^f^	Abclonal catalog # RK00074 or similar	100	Range: 23.4-1500 pg/ml Sensitivity: <6.3 pg/mL Specificity: 50 ng/mL Intra-assay precision: CV<10% Interassay precision: CV<15%	5.0

^a^ELISA: enzyme-linked immunosorbent assay.

^b^SAA: serum amyloid A.

^c^CV: coefficient of variation.

^d^Hcy: homocysteine.

^e^S100B: S100 calcium-binding protein B.

^f^BDNF: brain-derived neurotrophic factor.

The required materials for this procedure are the serum aliquots, ice, a fixed-angle centrifuge for 2 mL tubes, 1.5 mL protein low-binding tubes, tips, pipettes, 15 or 50 mL tubes (depending on the ELISA kit instructions), a 96-well plate shaker (if mentioned by the ELISA kit manufacturer), a 96-well plate mixer with heating (if mentioned by the ELISA kit manufacturer), and a multiplate reader.

Serum aliquots will be thawed on ice and then mixed gently. Samples will be centrifuged at 13000× *g* for 2 minutes at 4°C to remove the cell debris. The volume indicated in the kit manufacturer’s protocol will be taken. The instructions will be used for sample preparation and analysis. Measurements will be made in duplicate.

#### Calculation of Results

The optical density (OD) of each well will be read using a microplate reader set to 450 nm. The duplicate readings for each standard, control, and sample will be averaged, and the average 0 standard OD will be subtracted. A standard curve will be created by reducing the data using computer software capable of generating a 4-parameter logistic (4-PL) curve fit. Sample concentrations will be calculated from the equation. If samples have been diluted, the concentration read from the standard curve will be multiplied by the dilution factor.

### Power Calculation, Statistical Model, and Data Analysis

Based on previous studies, the power of the study, with an α of .05 and a power of 80%, the required number of cases and controls is 52 and 26, respectively, for a mean difference in 2 points (SD 3.0) in MOCA scales.

Statistics will be computed using IBM SPSS software version 28.0.1 or newer. Descriptive analysis of the baseline characteristics of the overall population by gender, age, and education will be conducted. Continuous variables will be presented as the mean (SD) or the median (IQR), and countable data will be presented as numbers and percentages. Comparisons of groups will be conducted using the t-test or the Wilcoxon rank-sum test based on the type of distribution of data and the homogeneity of the variance. The chi-square test or the Fisher exact probability method will be used for counting data, as appropriate.

Multiple linear and logistical regression analyses will be performed to evaluate the association between outcomes and potential risk factors identified in the questionnaires. Participants lost to follow-up will be treated as right-censored data. The Pearson coefficient will be used to assess the correlation between cognitive scores and serum levels of the studied biomarkers. A 2-sided significance level of .05 will be used for all primary and secondary analyses unless stated otherwise.

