**Methods:**

A case-control study will be conducted on at least 100 patients diagnosed with IBD, matched with 100 healthy individual controls. The matching will include sex, age, and education. Patients will be fully examined, and a full interview and a neurological and cognitive examination will be performed. The primary clinical outcomes will be cognitive test scores (Montreal Cognitive Assessment, Trail Making Test, Digit Symbol Substitution Test, forward and backward digit span testing). Depression, stress, and anxiety screening will also be performed. Blood samples from all participants will be collected, and aliquots will be immediately stored in a biobank. Primary laboratory outcomes will include serum levels of presumed cognitive dysfunction blood biomarkers SAA, Hcy, S100B, and BDNF. Follow-up will be performed at 12, 24, 36, and 48 months.

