## Methods

### Study Design

The study will be a single-center, prospective, observational, analytic study with a group of at least 100 patients with a diagnosis of certainty of IBD and a group of at least 100 HC. The study is part of a PhD thesis, and funding was obtained from the parent university.

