## Results

The collection of study data started in December 2021, and it is currently ongoing. Since the start of the study, 53 patients with IBD have been recruited and 50 HC were matched until the moment of this paper being published. The blood samples collected were stored according to the laboratory procedures. Data collection should end in January 2030. Intermediary analysis will be performed in April 2024 after the first 50 patients recruited go through the 12-month follow-up visit. Recruitment will continue until the number of participants in the IBD and HC groups is met (n=100 for each group).

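### The only power statement is a 2:1 MOCA calculation that does not match the planned 1:1 study of 100 per group, and it sizes one of about 35 implied primary tests that all share an unadjusted .05

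*Protocol article*

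**What the plan says.** The section on power and data analysis sets the error rates "with an α of .05 and a power of 80"% and concludes that "the required number of cases and controls is 52 and 26, respectively, for a mean difference in 2 points (SD 3.0) in MOCA scales". No other sample-size reasoning appears.

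The design is one control per patient. The Abstract (Methods) says "A case-control study will be conducted on at least 100 patients diagnosed with IBD, matched with 100 healthy individual controls"; Study Design plans "a group of at least 100 patients with a diagnosis of certainty of IBD and a group of at least 100 HC"; and Results says "Recruitment will continue until the number of participants in the IBD and HC groups is met (n=100 for each group"). Recruitment to date follows that ratio: "53 patients with IBD have been recruited and 50 HC were matched".

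The Abstract makes the cognitive scores (MOCA, Trail Making, Digit Symbol, forward and backward digit span) and four serum biomarkers primary. Table 1 adds, also as primary, MCI occurrence, the association of biomarkers with cognitive scores, and correlations involving IBD duration and type. On error control the protocol says: "A 2-sided significance level of .05 will be used for all primary and secondary analyses unless stated otherwise". Nothing else is stated.

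Results adds an early analysis: "Intermediary analysis will be performed in April 2024 after the first 50 patients recruited go through the 12-month follow-up visit". The publication plan says that this first phase, with 50 patients and 50 controls, will be published, and recruitment then continues to 100 per group.

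**The concern.** A sample-size statement should tell the reader what the planned study can detect. This one gives numbers for another allocation and another size, so the stated 80% power is not the power of this study, and the target of 100 per group has no stated basis. It also says nothing about the biomarker correlations, which carry the study's main claim about prediction.

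The second part concerns error control. Many outcomes are called primary, none is ranked, and each is judged at .05. Whichever crosses that line could be reported as a primary result, possibly first in the 50-per-group paper and again at the end. The Discussion would use such results to reconsider treatment strategies and to support serum markers for stratifying MCI risk, so a chance finding could carry real weight.

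**Working it through.** **Inputs.** From the power section: difference 2 MOCA points, SD 3.0, two-sided alpha .05, power 80%. From Study Design and Results: 100 per group. From Results and the publication plan: 50 per group at the early analysis.

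**Reproducing the stated figure.** With *k* cases per control, controls = (1 + 1/*k*)(1.96 + 0.8416)² (SD/difference)², and (1.96 + 0.8416)² = 7.849.
- *k* = 2: 1.5 × 7.849 × 2.25 = 26.5 controls and 53.0 cases. This matches 26 and 52 to within rounding.
- *k* = 1: 2 × 7.849 × 2.25 = 35.3, so 36 per group (36.3 by t-test, so 37).
- One-sided 2:1 gives 21 and 42, which does not fit.

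The stated figure is therefore a two-sided 2:1 calculation.

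**Power for 2 points.** SE = 3√(1/n₁ + 1/n₂); power = Φ(2/SE − 1.96).

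| Patients / controls | SE | Normal | t-test |
|---|---|---|---|
| 52 / 26 | 0.721 | 79.3% | 78.2% |
| 50 / 50 | 0.600 | 91.5% | 91.0% |
| 100 / 100 | 0.424 | 99.7% | 99.7% |

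Difference detectable with 80% power at 100 per group: 2.80 × 0.424 = 1.19 points. For a correlation within the 100 IBD patients: tanh(2.80/√97) = 0.28 at .05, and about 0.38 at .05/24.

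**Counting the primary tests.** The protocol gives no count; this one is derived:
- group comparisons of 6 scores (MOCA, TMT-A, TMT-B, DSST, forward span, backward span): 6
- group comparisons of biomarkers: 4
- MCI occurrence: 1
- biomarker-by-score Pearson correlations, 4 × 6: 24

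The total is 35. Adding the memory impairment score, which the Discussion summary lists, gives 7 + 4 + 1 + 28 = 40. Duration and type analyses would come on top.

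**False positives if all 35 nulls hold.**
- Expected number: 35 × .05 = 1.75, whatever the dependence.
- At least one, if independent: 1 − 0.95³⁵ = 83%.
- The tests are not independent. In a simulation at 100 per group, with assumed correlations of 0.3 to 0.7 between scores and 0.1 to 0.3 between markers, the chance of at least one falls to about 65% to 80%.

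**Two looks at one hypothesis.** With half the information at the first look (50 of 100 per group), the two statistics correlate at √0.5 = 0.707. Then 1 − P(|Z₁| < 1.96 and |Z₂| < 1.96) = 8.3%. At information fractions of 1/3 and 1/4 it is 8.8% and 9.1%.

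**Cost of adjustment.** Even with Bonferroni over 35 tests (.05/35 = .00143), 100 per group keeps about 93% power for 2 MOCA points (t-test). At 50 per group it would be about 52%.

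**The case against.** The best defence is that the stated numbers are minimum requirements and the plan exceeds them in both groups. That stands as far as it goes. A reader might infer that 52 and 26 is a miscalculation, or that the study is too small for MOCA. Neither is supported: the figure reproduces, the MOCA comparison between groups is planned, and its power at 100 per group is 99.7%. What is left is a power statement for a different design and an unexplained target.

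It can also be said that the count of 35 is ours, that the MCI objective is worded as description, and that the protocol does not list what is tested in April 2024. All three are fair. The count is therefore given as implied, and the 8.3% only as a condition: the same hypothesis tested at .05 on both occasions, with either result claimed. No early stopping for significance is planned, and formal alpha spending is more a convention of confirmatory trials than of an observational study.

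A reader might also infer that a false primary finding is almost certain. The 83% needs independence, which these overlapping tests lack; about 65% to 80% is more realistic.

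Finally, a separate analysis plan could add an adjustment. But the protocol does not leave the matter open: it fixes .05 for all primary and secondary analyses, with no exception stated.

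**Conclusion.** The point holds in a limited form. The sole power statement describes a 2:1 comparison of 52 and 26 with 78% to 79% power. The planned 1:1 study of 100 per group has 99.7% power for the same difference and 80% power for about 1.2 points. The mismatch harms the justification of the design, not the MOCA comparison.

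The more serious consequence is the flat .05 across an unranked primary list. It implies 1.75 expected false positives over about 35 tests if nothing is related to anything, and a chance of at least one of about 65% to 80%. These figures rest on our count of tests and on assumed correlations, since the protocol gives neither. The 8.3% for two looks assumes half the information at the first and a claim made from either. This should be corrected, but it does not threaten the feasibility of the study.

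**What to change.** - **Power.** Restate it for 1:1 and 100 per group: 99.7% for 2 MOCA points (SD 3.0), 1.2 points detectable at 80%, and r of about 0.28 within the IBD group at unadjusted .05.
- **Primary.** Name the baseline MOCA group comparison, the one outcome that was sized, as the single primary at two-sided .05.
- **Other group comparisons.** Put the remaining scores, the four biomarkers and MCI occurrence under Holm.
- **Correlations.** Put the biomarker-by-score, duration and type analyses under Benjamini-Hochberg at 5%.
- **April 2024 analysis.** Label it descriptive, with the confirmatory test made once, at 100 per group. No alpha then needs to be split between the two analyses.

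Cost: no change in enrolment, but fewer results will be called significant. The study is registered and already recruiting (53 patients and 50 controls), so the change of primary outcomes must be a dated, documented amendment.
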